**Fig. 2 Fig2:**
[figure not shown]
Recruitment projections

**Fig. 3 Fig3:**
[figure not shown]
HEALTH Gantt

### Statistical analysis

We will base all analyses on the intention-to-treat principle, analysing women in the groups to which they are randomised. We will conduct all study analyses according to a statistical analysis plan agreed in advance by the Trial Steering Committee. We will conduct the analyses at two-sided 5% significance level with corresponding 95% confidence interval generated as appropriate. Full details may be found in the separate statistical analysis plan.

We will conduct the analysis of the two co-primary outcomes (patient satisfaction and MMAS) independently. We will analyse patient satisfaction (‘totally satisfied’ vs others) using a logistic regression model with adjustment for minimisation factors. We will use a complete-case analysis for the main analyses, with no imputation for missing data. Sensitivity analyses will assess the impact of varying the dichotomisation cut-off and adjusting for clustering at centre and surgeon levels. Sensitivity analyses (such as using a multiple imputation approach) will also explore what influence missing data might have on the robustness of our findings and where feasible modelling non-ignorable (informative) missing data mechanisms. A further analysis of patient satisfaction will use a proportional odds model utilising the underlying ordinal (Likert) scale (Ologit function, Statacorp, 2012). We will analyse the MMAS using linear regression adjusted for baseline and minimisation factors or an ordinal model if the data are found to be skewed. We will analyse secondary outcomes using generalised linear models adjusted for minimisation factors (and, when appropriate, a baseline measure).

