### Randomisation and allocation

Eligible and consenting participants are randomised to one of the two study groups in a 1:1 allocation ratio using the randomisation application at the trial office at the Centre for Healthcare Randomised Trials (CHaRT). This randomisation application is available 24 h a day, seven days a week as both an interactive voice response (IVR) telephone system and as an Internet-based application. The randomisation will use a minimisation algorithm based on centre and age.

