### Follow-up procedures

Eligible patients who have provided signed informed consent to participate in the study will complete the SF12, Menorrhagia Multi-Attribute Quality of Life Scale (MMAS) and EQ5D at baseline before being randomised to either LASH or EA. They will also complete a diary for days 1–14 post surgery, to record pain scores and the use of analgesics. At six weeks after surgery, participants will complete a questionnaire to measure Pain Numerical Rating Scales (NRS), time to return to normal activities and acceptability, EQ5D and SF12. At six months after surgery and at 15 months following randomisation, participants will complete the SF12, MMAS, EQ5D, satisfaction with treatment and questions about healthcare utilisation. Participants will receive up to two reminders by post, email or phone, taking into account any preferences they may have for mode of communication.

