#### Primary outcome measure

The co-primary (clinical) outcomes will be: (1) MMAS, a condition-specific QoL outcome [13] in the range of 0–100 based upon six domains, measured at 15 months after randomisation; and (2) patient satisfaction, measured on a 6-point scale (from ‘totally satisfied’ to ‘totally dissatisfied’) measured at 15 months after randomisation. Mean (SD) MMAS scores will be reported provided the data are normally distributed. Satisfaction will be treated as a binary variable: ‘totally satisfied’ vs other responses. We will address these two co-primary outcomes in a hierarchical fashion. First, we will consider the patient satisfaction, and if this shows a statistically significant difference (*p* < 0.05), then we will consider the disease-specific QoL MMAS outcome. Both will need to achieve statistical significance at *p* < 0.05 for the null hypothesis to be rejected. By specifying this hierarchy, we do not need to apply any adjustment for multiple comparisons, since the overall false-positive error is controlled at an alpha of 0.05. Together these measures are comprehensive, intuitive and accepted by patients and the clinical community and have been used in previous trials and studies by the Aberdeen group and others in the field [14–16].

The primary economic outcome is the incremental cost (to the health service) per quality-adjusted life year (QALY) gained (LASH vs EA). We will calculate this from within-trial health service costs (resource use collected via CRFs and patient questionnaires, and valued using standard unit prices) and generic QALYs (derived from responses to the EQ-5D). We will derive the incremental cost per QALY gained for LASH vs EA from generalised linear regression models adjusting for baseline health status and other important covariates.

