## Sample size, proposed recruitment rate and milestones

### Sample size

The specification of the target difference was driven by two criteria: (1) what target difference would be important if it existed; and (2) what would be a realistic difference [17] given the interventions under evaluation. With regards to (2), the observed rates in the recent IPD meta-analysis of abdominal hysterectomy vs first-generation EA [6] would lead to a target difference of odds ratio (OR) of 2.84 (95% vs 87%) for patient satisfaction. Such an OR also equates to a medium-sized standardised effect (Cohen’s d). This requires 292 participants per group for a two-sided test with 90% power. This size would also be more than sufficient to allow a small- to medium-sized (0.3, Cohen’s d) standardised effect in the co-primary outcome, MMAS, to be detected; this is a target difference for MMAS that can be viewed as important and has observed in other areas for similar outcomes. This would equate to being able to detect a target difference of 10 points on the 0–100 scale, given a standard deviation of 33 points or less. Given these assumptions for the co-primary outcomes, and additionally allowing for 10% missing data, 648 participants in total are required.

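### Adding baseline MMAS to the satisfaction model would be a cheap gain in efficiency on the gatekeeper test; its omission is not an error

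*Protocol article*

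**What the plan says.** The Statistical analysis section of the protocol article gives the satisfaction model as logistic regression, "using a logistic regression model with adjustment for minimisation factors". Under Randomisation and allocation these factors are two: "The randomisation will use a minimisation algorithm based on centre and age". For the other co-primary the same section says "We will analyse the MMAS using linear regression adjusted for baseline and minimisation factors".

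Baseline MMAS is planned for every consenting woman. Under Follow-up procedures, participants complete the SF12, "Menorrhagia Multi-Attribute Quality of Life Scale (MMAS) and EQ5D at baseline before being randomised to either LASH or EA". Table 1 confirms MMAS at baseline and shows satisfaction only at six and 15 months, so satisfaction has no baseline value of its own.

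The order of testing is set under Primary outcome measure: "First, we will consider the patient satisfaction, and if this shows a statistically significant difference", MMAS is then considered, and both must reach p < 0.05. The endpoint is the top category of a six-point scale: "Satisfaction will be treated as a binary variable: ‘totally satisfied’ vs other responses". The Sample size section uses a "target difference of odds ratio (OR) of 2.84 (95% vs 87%) for patient satisfaction", with 292 per group, a two-sided test and 90% power. The main analysis uses complete cases and does not impute.

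**The concern.** The outcome tested second is adjusted for baseline severity and the outcome tested first is not. MMAS is the natural severity variable here, because the Background defines heavy menstrual bleeding by its interference with quality of life. Severity at entry may well bear on how satisfied a woman is 15 months later. If it does, adjusting for it raises the power of the treatment test and removes the effect of a chance imbalance in severity, against which minimisation on centre and age gives no protection.

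Power matters most on this test, because a miss on satisfaction closes the route to MMAS. The article names the covariates of this model, so the point concerns a stated choice and not a detail left to the statistical analysis plan.

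**Working it through.** **1. The plan's own figure.** Inputs from the Sample size section: 0.95 and 0.87, two-sided 5%, 90% power. The mean proportion is 0.91.

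n = [1.960·√(2·0.91·0.09) + 1.282·√(0.95·0.05 + 0.87·0.13)]² / 0.08² = (0.793 + 0.514)² / 0.0064 ≈ 267 per group.

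With the continuity correction: n/4 · [1 + √(1 + 4/(n·0.08))]² ≈ 292, an exact match. The odds ratio is (0.95·0.13)/(0.05·0.87) = 2.84. Allowing for 10% missing, 292/0.9 = 324.4, and 2 × 324 = 648. The stated size therefore stands and takes no credit for covariates. Without the continuity correction, 292 per group gives 92.4% power.

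**2. Gain from a prognostic covariate.** The documents give no correlation r between baseline MMAS and satisfaction, so r is an assumed range. Two approaches were used at 87% v 95%:

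- Approximation: effective n = 292/(1 − r²), put into the two-proportion power formula.
- Simulation: 292 per arm, logistic models with and without one standardised covariate, Wald test, 6000 replicates per setting, minimisation factors not modelled. The Monte Carlo standard error of each power figure is √(0.93·0.07/6000), about 0.3 points.

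Here r is the correlation with the observed binary outcome.

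| r (approximation) | effective n | power | r (simulation) | power without | power with |
|---|---|---|---|---|---|
| 0 | 292.0 | 92.4% | 0.00 | 92.7% | 93.0% |
| 0.1 | 294.9 | 92.6% | 0.10 | 93.2% | 93.6% |
| 0.2 | 304.2 | 93.4% | 0.22 | 93.2% | 94.1% |
| 0.3 | 320.9 | 94.5% | 0.30 | 93.2% | 95.2% |
| 0.4 | 347.6 | 95.9% | 0.40 | 93.2% | 96.7% |

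The gain is one point or less up to about r = 0.2, about 2 points at 0.3 and about 3.5 points at 0.4. At r = 0 nothing is lost.

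**3. Scale of the correlation.** If r is instead defined on a latent normal satisfaction scale, the same nominal value means less. At 87% a latent 0.5 is only about 0.31 on the binary outcome. A latent-normal simulation (5000 trials per setting) gave gains of 0.3, 0.5, 1.7 and 2.2 points at latent r of 0.2, 0.3, 0.4 and 0.5. The two sets agree once put on one scale: 2.2 points at 0.31 against 2.0 at 0.30.

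**4. Less extreme rates (assumed).** At 60% v 70%, the approximation gives 71.8% power unadjusted and gains of 0.4, 1.7, 4.0 and 7.3 points at binary r of 0.1, 0.2, 0.3 and 0.4. At 50% v 62%, the latent-normal simulation gives gains of 1.0, 1.8, 3.2 and 5.9 points over about 83% at latent r of 0.2 to 0.5.

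**5. Two side effects.** Suppose a fraction m of women lack baseline MMAS and drop out of the adjusted model. The effective size is 292(1 − m)/(1 − r²), so the gain is cancelled when r² = m: at r = 0.14 for 2% missing and r = 0.22 for 5%. Separately, the odds ratio becomes conditional on baseline MMAS. In the simulation it was 3.12 at r = 0.30, against the marginal 2.84.

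**The case against.** The strongest objection is that the plan contains no mistake. Adjusting for the minimisation factors matches the randomisation. MMAS is adjusted for its own baseline because it has one; satisfaction with treatment cannot have one. The different covariate sets are therefore not an inconsistency, although a reader might infer one.

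A reader might also infer that the plan gives up power at no cost, or that the gatekeeper test is underpowered. The documents support neither reading. The loss depends on a correlation they do not report, in women already selected for heavy bleeding, failed medical treatment and eligibility for ablation. The planned test meets its 90% without the covariate. Nor is the change free as it stands. Baseline questionnaires may come back by post, and under the complete-case rule a missing baseline score would remove a woman from the gatekeeper analysis. The estimand of the odds ratio also changes.

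All of this stands as a limit on the point's size. It does not remove the point. A useless covariate costs essentially no power, a simple rule for missing baseline values keeps every observed outcome in the model, and a standardised risk difference preserves the marginal reading. The larger gains at 60% v 70% or 50% v 62% remain illustrations, since the article gives no rate for the top satisfaction category beyond the planning figures.

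**Conclusion.** The point holds as an optional improvement, not a correction. The gatekeeper model leaves out a plausibly prognostic severity score that the trial already plans to collect and already uses for its other co-primary. The stated 292 per group, 648 in total and 90% power are unaffected.

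At 87% v 95% the expected gain is about 0 to 2 points of power for an assumed correlation of 0 to 0.3, and about 2 to 3.5 points at 0.4 to 0.5, depending on the scale. It would be larger only if the true totally satisfied rates were less extreme than planned. Protection against chance imbalance in severity is a further benefit and likewise depends on baseline MMAS being prognostic. Both the correlation and any alternative rates are assumptions.

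**What to change.** In the Statistical analysis section, or in the statistical analysis plan to which it refers, pre-specify before database lock:

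- Baseline MMAS as a continuous covariate, with the minimisation factors, in the satisfaction logistic model and in the proportional-odds analysis.
- A rule for missing baseline MMAS that uses no outcome data, for example single mean imputation of the covariate, so that no woman with an observed satisfaction response is dropped.
- A standardised risk difference reported beside the conditional odds ratio.
- The model with minimisation factors only, kept as a sensitivity analysis.

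The cost is one covariate, one missing-baseline rule and one extra summary measure, with no new data. The downside is that the main odds ratio becomes conditional on baseline MMAS and is no longer directly comparable with the 2.84 used for sizing.

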### Planned subgroup analyses

We will perform exploratory subgroup analyses for the following groups: uterine cavity length (8 cm ≤ vs > 8 cm); menstrual pain (dysmenorrhoea) at baseline (‘severe’ vs non-‘severe’ – determined using a 5-point Likert scale); fibroids (present or absent); patient age < 40 or > 40 years. We will conduct the pre-specified subgroup analyses by including the corresponding treatment by subgroup interaction term in the corresponding regression models for the co-primary outcomes (patient satisfaction and MMAS). No other subgroup analyses are planned. We will state the subgroup analyses as exploratory and evaluate at the 5% two-sided significance level.

### Proposed frequency of analyses

We will perform a single statistical analysis when 12-month follow-up data have been collected. An independent Data Monitoring Committee will review confidential interim analyses of accumulating data at its discretion but at least annually.

## Economic evaluation

The economic analysis will consist of a trial based analysis of individual patient level cost and effect (QALY) data and a decision modelling component to inform cost-effectiveness in the longer term.

For the within-trial analysis, we will estimate total costs to the health service, wider costs to society associated with lost productivity and QALYs for each individual patient enrolled in the RCT. We will estimate costs of the initial intervention procedures from resource use data recorded on the CRFs of each individual patient (including time in theatre, staff present, any perioperative complications and length of stay in hospital post treatment) coupled with routine unit cost data [12, 18]. We will also value any subsequent contacts with primary and secondary care (collected from patient questionnaires at six months after surgery and 15 months after randomisation), for each patient using nationally accepted sources of unit costs. Since the EQ-5D is the recommended instrument for deriving QALY weights by NICE (https://www.nice.org.uk/process/pmg9/chapter/foreword), we will use participant responses to this instrument (at baseline, six weeks and six months after surgery and 15 months after randomisation) to derive QALYs. The SF-12 is being included as another potentially more sensitive measure of general health-related QoL and will provide an alternative means for estimating QALYs via the SF-6D scoring algorithm. We will undertake this as a sensitivity analysis at 12 months. Productivity losses will be estimated based on the reported time taken to return to normal activities (assessed at six weeks after surgery) and responses to work productivity questions at six months after surgery and 15 months after randomisation. We will value time lost from paid employment using national age-/sex-specific average gross wage rates [19]. We will estimate the value of time lost from alternative non-paid activities using appropriate shadow prices.

Analysis of the patient level cost and QALY data will use appropriately specified generalised linear regression models adjusted for baseline EQ-5D score and minimisation factors applied during randomisation [20]. From these analysis models, the co-efficient for the treatment allocation group will provide estimates of the incremental costs and QALYs associated with LASH vs EA. We will characterise uncertainty surrounding the joint estimates of incremental costs and effects by running the regression models on a large number of bootstrapped samples obtained, with replacement, from the original trial sample. This process will generate a large number of estimates of the incremental costs and effects, capturing any correlation between them. We will plot these results on the incremental cost-effectiveness plane and use them to derive a cost-effectiveness acceptability curve, indicating the probability of LASH being cost-effective (at 12 months) given different notional values of decision-makers’ willingness to pay per QALY gained. The primary analysis will assess cost-effectiveness from the health service perspective, but we will also conduct a secondary analysis incorporating wider costs to society. As a further step to help present the 12-month findings in a meaningful way for decision-makers, we will present all costs and outcomes within a cost–consequence balance sheet. This will summarise all the costs and trial outcomes by treatment allocation group and indicate which treatment group each outcome favours.

While the within-trial analysis will be useful for informing cost-effectiveness in the short term, previous research suggests that a longer time horizon may be required to determine the relative cost-effectiveness of LASH vs EA [8], as a result of EA being less costly and effective in the short term but associated with higher failure rates and subsequent surgery beyond 12 months. Therefore, we will develop a simple Markov model to simulate the recurrence of symptoms and need for subsequent treatment over time, in order to estimate cost-effectiveness in the longer term. We will construct the model in consultation with clinicians and based on a review of existing decision models developed in the field. Input parameters will initially be informed by the within-trial analysis (to determine initial treatment costs and outcomes and the probability of any subsequent treatment events/complications occurring within 12 months). This will be supplemented with published data on recurrence and the need for further gynaecological surgery (repeat EA, LASH or conventional total hysterectomy) following EA and LASH. The model will incorporate the initial health service costs of treatment, ongoing costs associated with successful and unsuccessful treatment, and costs associated with subsequent surgery. We will apply utility weights (obtained from the trial data) to the alternative states in the model, allowing modelled QALYs to be estimated. We will run the model over a five-year period (the time point by which most women would be expected to have completed any subsequent required treatment), though we will also explore the impact of adopting longer time horizons. Linkage of participants’ records to health episode statistics will allow future quantification of the incidence of repeat gynaecological surgery, providing a means for validating/updating initial model based predictions.

We will carry out probabilistic and deterministic sensitivity analysis to characterise the uncertainty surrounding the model based estimates of incremental costs and effects of LASH vs EA. For the Probabilistic Sensitivity Analysis (PSA), we will assign an appropriate distribution to each model input parameter (reflecting the degree of uncertainty surrounding it due to sampling variation) and we will analyse the model a large number of times, each time randomly drawing a value for each input parameter from its assigned distribution [21]. This process will generate a large number of estimates of the incremental costs and effects. We will use cost-effectiveness acceptability curves to summarise the findings from the PSA. Further deterministic analysis will assess the sensitivity of the model based estimates to further choices over sources of parameter estimates and any structural assumptions required when constructing the model.

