#### Secondary outcome measures

Patient-reported: MMAS score at six months after surgery; patient-reported satisfaction at six months after surgery; acceptability of procedure measured at six weeks after surgery; severity of postoperative pain using a pain NRS measured at 1–14 days and six weeks after surgery; symptom diary days 1–14 after surgery (including analgesic use); generic health-related QoL (SF-12, EQ-5D 3-L) measured at six months after surgery and at 15 months after randomisation. We will describe outcomes using mean (SD) or frequency (%) as appropriate.

Clinical: duration of operation; perioperative complications and recovery details including analgesia requirements; time to discharge; further gynaecological surgery by 15 months after randomisation. We will describe outcomes using mean (SD) or frequency (%) as appropriate.

Economic: wider societal costs associated with changes in productivity based on information on the time taken to return to normal activities (following intervention) combined with questions on work productivity delivered during the follow-up period. Furthermore, we will develop a simple Markov model, based on within trial data supplemented by available published data on the requirement for further gynaecological surgery over time (following the alternative procedures) and use it to extrapolate cost-effectiveness beyond 15 months after randomisation.

While the analyses within this application are based upon an initial 15 months after randomisation follow-up, we also anticipate collecting long-term information on further gynaecological surgery by utilising Hospital Episode Statistics for England and Wales and Information Services Division (ISD) data for Scotland. We will use these data in the future to revise the extrapolated longer-term estimates of cost-effectiveness for LASH vs EA.

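### Time to return to normal activities is asked only at six weeks, so it is right-censored at about 42 days for women not yet recovered, and the stated generalised linear models do not handle this

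*Protocol article*

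**What the plan says.** Under Follow-up procedures the protocol article states: "At six weeks after surgery, participants will complete a questionnaire to measure Pain Numerical Rating Scales (NRS), time to return to normal activities and acceptability". Table 1 (Schedule of data collection) marks the item in the six-week column only; it does not recur at six or 15 months.

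The item is used in the economic work. Secondary outcome measures lists, under the economic heading, "wider societal costs associated with changes in productivity based on information on the time taken to return to normal activities". Economic evaluation says "Productivity losses will be estimated based on the reported time taken to return to normal activities (assessed at six weeks after surgery") and, in the same sentence, adds a second source: "responses to work productivity questions at six months after surgery and 15 months after randomisation". Time lost from unpaid activities is to be valued separately with shadow prices.

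On models, Statistical analysis gives one general rule: "We will analyse secondary outcomes using generalised linear models adjusted for minimisation factors", with a baseline measure added where appropriate. Economic evaluation says "Analysis of the patient level cost and QALY data will use appropriately specified generalised linear regression models". The health-service perspective is primary; beyond it, "we will also conduct a secondary analysis incorporating wider costs to society". The article does not say how a woman who has not returned by six weeks is coded or analysed. It refers to a separate statistical analysis plan for full details.

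**The concern.** A duration asked about once, at a fixed time, is known only for those whose event has already happened. For the others the data say only that it exceeds about 42 days. A mean or a generalised linear model for a mean needs a number for every woman, so unrecovered women must be left out, given the value 42, or imputed. Leaving out or capping shortens the mean in whichever arm has more of them.

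This matters because recovery is part of the trial's rationale. The Background weighs the effectiveness of conventional hysterectomy against its prolonged recovery and presents LASH as avoiding that penalty. A measure that stops at six weeks cannot show how long slow recoveries last. Two results are exposed: any comparison of recovery time, and the societal-cost analysis, above all its unpaid-time component.

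Most of this cannot be left to the analysis plan. That plan can choose a model that handles censoring, but it cannot supply a return date that no questionnaire asks for.

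**Working it through.** **Inputs from the article.** The item is asked once, six weeks after surgery, so c = 6 × 7 = 42 days. The stated model class is generalised linear. The article gives no mean, median, spread or proportion unrecovered at six weeks for either arm, so there is no figure of its own to reproduce. The sample size concerns the co-primary outcomes and has no bearing here.

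**Assumptions.** Times to return are lognormal with log-SD s of 0.6 or 0.8, EA median 7 or 14 days, and LASH median 14 to 42 days, always longer than EA. These are illustrative and do not come from the article.

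**Formulas.** For median m, let a = ln(c/m)/s, F = Φ(a) and P = m·exp(s²/2)·Φ(a − s).

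- Full mean: m·exp(s²/2)
- Unrecovered at c: 1 − F
- Mean with times capped at c: P + c(1 − F)
- Mean with unrecovered women dropped: P/F

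**Worked case: s = 0.6, EA median 7, LASH median 28.**

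- LASH: full mean 28 × exp(0.18) = 33.52; a = ln(1.5)/0.6 = 0.676; F = 0.7504, so 25.0% are unrecovered. P = 33.52 × 0.5302 = 17.77. Capped mean = 17.77 + 42 × 0.2496 = 28.26; dropped mean = 17.77/0.7504 = 23.69 (unrounded inputs).
- EA: full mean 8.38, unrecovered 0.1%, capped mean 8.37, dropped mean 8.32.
- LASH minus EA: full 25.1 days; capped 19.9 (21% short); dropped 15.4 (39% short).

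**Range over the assumed grid.**

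| Case | Unrecovered at 42 days, EA / LASH | Full difference | Capped | Dropped |
|---|---|---|---|---|
| s = 0.6, medians 7 and 14 | 0.1% / 3.4% | 8.4 | 8.0 (5% short) | 7.1 (15% short) |
| s = 0.6, medians 7 and 28 | 0.1% / 25.0% | 25.1 | 19.9 (21% short) | 15.4 (39% short) |
| s = 0.8, medians 14 and 42 | 8.5% / 50.0% | 38.6 | 15.9 (59% short) | 9.4 (76% short) |

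The first and last rows are the extremes of the grid.

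**Check with another shape.** Assume exponential times with EA mean 10 days. The capped mean is m(1 − e^(−c/m)), and the mean among those returned is (m − (c + m)e^(−c/m))/(1 − e^(−c/m)).

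- LASH mean 21: full difference 11; capped 18.16 − 9.85 = 8.3; dropped 14.43 − 9.36 = 5.1.
- LASH mean 28: full difference 18; capped 21.75 − 9.85 = 11.9; dropped 15.94 − 9.36 = 6.6.

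Both cases lie inside the range above.

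**What a capped mean estimates.** If every woman is observed to 42 days, the capped mean is exactly the restricted mean time to 42 days. It falls short only as an estimate of full recovery time. Reported as a restricted mean it is sound, though it leaves out whatever is lost after day 42.

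**The case against.** The strongest reply has four parts.

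- **Productivity loss does not rest on the six-week item alone.** The sentence goes on to name work-productivity questions at six and 15 months. This stands for paid work: loss after six weeks may be picked up there, and a bias in total societal cost is not shown. The wording of those questions is not given, so their coverage of unpaid activity cannot be judged. Nothing suggests that they yield a date of return to normal activities.
- **No wrong method is fixed for this item by name.** The rule on generalised linear models is general. Time to return is named only as an economic input, though the recovery details listed among the clinical outcomes might cover it. The complete-case sentence sits in the text on the co-primary outcomes. Coding and a censoring method may be in the questionnaire or the analysis plan, neither of which is shown. This also stands: dropping or capping is a possibility, not something the article states. The single collection point, however, is stated, and no later document on analysis can undo it.
- **Direction and size are assumed.** A reader might infer that censoring falls mainly on LASH and that the plan therefore flatters it. The article does not support this as fact. It attributes prolonged recovery to conventional hysterectomy, describes LASH recovery as rapid, and gives no times by arm.
- **The reach is limited.** The societal perspective is a secondary analysis. This stands in full.

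**Conclusion.** The point holds as a conditional one. The article fixes a single six-week observation of time to return to normal activities. Women not yet recovered are therefore right-censored at about 42 days, and the only stated model class does not accommodate that. If more LASH than EA women are unrecovered at six weeks, and if they are dropped or capped, the difference in full recovery time and in unpaid time lost will be understated. Under the assumed lognormal times the shortfall is about 5% to 59% with capping and 15% to 76% with dropping. The low end corresponds to 3.4% of LASH women unrecovered and the high end to half of them. The true size is unknown. If recovery is nearly complete by six weeks in both arms, the effect is small.

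The consequence is confined to the recovery comparison and the secondary societal-cost analysis. Patient satisfaction, MMAS and the health-service cost per QALY do not depend on this item.

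**What to change.** 1. Record a woman who has not returned to normal activities on the six-week questionnaire as censored at the date she completes it, distinct from a missing answer.
2. Compare arms with a time-to-event model adjusted for the minimisation factors (centre and age). Alternatively, report a restricted mean to 42 days and label it as such, so that it is not read as full recovery time.
3. Repeat the return-date item in the existing six-month questionnaire for women who had not returned at six weeks, and use that date in the productivity costs. State how it combines with the six-month work-productivity answers so that paid time is not counted twice.
4. Report the number and proportion not yet returned at six weeks by arm. This shows directly whether the issue is large or negligible.

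The cost is one extra item in a questionnaire already being sent, and a different model. The article reports recruitment still open, so later participants can supply the date. Women already past six months contribute censored times only, so completeness will vary with date of entry; the time-to-event analysis can accommodate this, but it should be reported.
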